#### **3.2 Secondary Objectives**

The secondary objectives of this study are to evaluate, across child age 6 weeks to 2 years, the impact of a SNHV program offered to vulnerable Australian mothers on:

1. Maternal: Pregnancy outcomes, Quality of Life, Mental health, Parent wellbeing, General Health, Parenting self-efficacy, and Health service use;
2. Child: General health and functioning;
3. Sibling: Mental health/behaviour; and
4. Nurse: Ability to effectively engage with parents and Use and knowledge of evidence-based clinical strategies.

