| Assessment Quality of Life (AQoL-8)                                                                                      | Self-reported multi-attribute utility health-related quality of life instruments for use as utility instruments which measure quality of life.                                                                                                |
| Maternal mental health: Depression, Anxiety, Stress Scale (DASS-21)                                                      | Three self report scales designed to measure the negative emotional states of depression, anxiety and stress.                                                                                                                                 |
| Parenting Wellbeing Index (PWI)                                                                                          | Self report questions about life satisfaction with 8 specific life domains. The domains are theoretically embedded, as representing the first level deconstruction of the global question: 'How satisfied are you with your life as a whole?' |
| General Health Questionnaire (GHQ-S1)                                                                                    | Single self report item assessing overall health                                                                                                                                                                                              |
| Parenting self-efficacy                                                                                                  | Self report items drawn from the Millennium Cohort Study, assessing how the mother feels about her life so far, e.g. the extent to which she feels that she gets what she wants out of life, feels in control and can run her own life.       |
| Health service use                                                                                                       | Self report questions designed for the study in consultation with investigators [name] and [name] (right@home health economists)                                                                                                                 |

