## 6.2 Eligibility Criteria

There have been a number of considerations in establishing the eligibility criteria and thus the recruitment strategy for the right@home trial. These include:

1. Longitudinal research about antenatal predictors of maternal and child outcomes. One of the key findings from CCCH's first literature review (**Appendix 3**) was that home visiting programs are more effective for families of low socioeconomic backgrounds. However, SNHV trials typically recruit based on a small number of risk factors (e.g. teenage parent, poverty). As such, it is not possible to say whether women with other known risk factors for poorer child development and learning outcomes may benefit from SNHV programs. For example, Chittleborough et al (2012) found that antenatal maternal factors such as teenage parent, single parent, low education, perinatal depression, poverty and smoking were strongest predictors of poor parent-infant related outcomes. PREview (<http://www.chimat.org.uk/preview/evidence>) indicates that postnatal (child 9 months) maternal predictors of child health, learning and behavioural outcomes at age 5 years were low income, low education, poor general health and low self efficacy. Following from this, we selected the risk factors to be tested by the recruitment pilot to encompass a range of socioeconomic and psychosocial characteristics.

2. Important "success" factors in previous SHNV trials relate to cohort "vulnerability". Summaries of the SNHV literature point to the added value of these programs for more vulnerable families, particularly those with low psychological resources and supports. Research reviews have also recognised that, while the most vulnerable might be those most likely to benefit, they are also hardest to recruit and retain in studies. Risk factors cluster together and, for the purposes of the right@home trial, we are assuming that the greater number of risk factors a woman has, the more 'vulnerable' she is.

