| Parenting self-efficacy                                              | X          |    |    | X  |     | X  |
| Health service use                                                   |            | X  | X  | X  | X   | X  |
| Health literacy                                                      |            |    | X  |    | X   |    |
| Parenting styles                                                     | X          |    |    | X  |     | X  |
| Child                                                         |            |    |    |    |     |    |
| Mental and general health                                            |            |    |    |    |     | X  |
| General Health                                                       |            | X  | X  | X  | X   | X  |
| Sibling                                                       |            |    |    |    |     |    |

| Study Measure                                           | Time point |    |    |    |     |    |
|---------------------------------------------------------|------------|----|----|----|-----|----|
|                                                         | Enrol      | 6w | 6m | 1y | 18m | 2y |
| Mental health/behaviour                                 | X          |    |    | X  |     | X  |
| Nurse                                            |            |    |    |    |     |    |
| Use and knowledge of evidence-based clinical strategies | X          | X  | X  | X  | X   | X  |
| MONITORING VARIABLES                                    |            |    |    |    |     |    |
| Maternal social capital/sensitive issues                | X          |    |    | X  |     | X  |
| Child birth data                                        |            | X  |    |    |     |    |
| Child growth data (e.g. height & weight)                |            | X  | X  | X  | X   | X  |
| Intervention dose and fidelity                          |            | X  | X  | X  | X   | X  |

Time points: w=week, m=month, y=year. Enrolment will occur within a fortnight of screening at the antenatal hospital clinic. Monitoring items are variables that may be used to describe the sample or to control for potential confounding and are not collected as demographics.

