## **10.3 Statistical Analysis Plan**

The frequency and patterns of missing data will be examined and sensitivity analyses will be performed comparing the results of analyses restricted to families with complete data and analyses where missing data are imputed using a conservative approach.

The baseline characteristics of the mothers will be presented for each treatment arm using the mean, median and IQR for continuous data and proportions for categorical data. Maternal and child outcome measures will be similarly described by treatment arm and comparisons made using the t-test and non-parametric tests for continuous data and the chi-squared test for categorical data.

Linear and logistic regression modelling will be conducted to test the primary and secondary hypotheses listed below, taking into account maternal baseline and child characteristics identified *a priori* i.e. child gender, socio-demographic characteristics of the mother and family, and maternal specific characteristics including health, mental health and self efficacy.

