### Objectives/hypotheses:

Primary: At child age 2 years, compared with the usual care group, intervention mothers will demonstrate:

1. Improved parent care, i.e. the parent's ability to provide a consistent, regular and supportive environment for their child;
2. Improved parent responsiveness, i.e. the parent's ability to tune in to their child's needs and to respond appropriately; and
3. A more supportive home environment, i.e. building a strong home learning environment through structured developmental promotion activities focusing on language.

Secondary: At child age 2 years, compared with the usual care group, intervention mothers will demonstrate:

1. Maternal: Improved pregnancy outcomes, Quality of Life, Maternal mental health, Parent wellbeing, General Health, Parenting self-efficacy, Health literacy, and more effective Health service use. The latter will depend on the service, e.g. preventative healthcare and

management vs. emergency department visits, and will be determined in partnership with the study health economists.

2. Child: Improved mental and general health, and language
3. Sibling: Improved mental health/behaviour
4. Nurse: Increased use and knowledge of evidence-based strategies

We have not powered the trial to consider subgroups but there will be some analyses which will need to be restricted to a subgroup of the trial, e.g. anything that refers to current parenting attitudes or behaviours (as not all women will already have children). These subgroup analyses will only be powered for larger effect sizes than the primary outcomes, and will be provided in a future ethics modification once the final outcome measures are decided. Another subgroup analyses which the team may consider (and, again, power will be limited) is testing whether the findings appear to be consistent by site/state.

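### The secondary outcome labelled parenting self-efficacy is described by items on the mother's control over her own life, so the parenting hypothesis has no matching measure as described

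*Protocol*

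**What the plan says.** Table 2 (Section 4.4) lists parenting self-efficacy among the maternal secondary outcomes. Its description reads "Self report items drawn from the Millennium Cohort Study, assessing how the mother feels about her life so far", followed by examples: "the extent to which she feels that she gets what she wants out of life, feels in control and can run her own life".

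The same label appears in four other places:
- the Synopsis, under Outcomes;
- Section 3.2, where the maternal objectives include "Mental health, Parent wellbeing, General Health, Parenting self-efficacy, and Health service use";
- Table 4 (Section 7), where "Parenting self-efficacy" is scheduled at enrolment, 1 year and 2 years;
- the secondary hypotheses in Section 10.3, which expect improvement at child age 2 years in "Maternal mental health, Parent wellbeing, General Health, Parenting self-efficacy, Health literacy, and more effective Health service use".

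Elsewhere the Protocol drops the word parenting. Section 10.3 lists, among the characteristics to be taken into account in the regression models, "maternal specific characteristics including health, mental health and self efficacy". Section 6.2 cites maternal predictors of child outcomes at age 5 years as "low income, low education, poor general health and low self efficacy".

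**The concern.** The label and the described content are different constructs. Parenting self-efficacy is a mother's confidence in her ability as a parent. The items described ask whether she feels in charge of her own life. A mother may score high on one and low on the other, and a program may move one without the other.

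What is at stake is the conclusion drawn. Section 2 presents home visiting as a way of making parents confident in caring for their children, and Section 5.1.1 gives the nurse the task of building parenting skills. A reader of the results would therefore take this outcome as evidence on parenting confidence. Under the present label, a difference between arms would be reported as a gain in parenting confidence, and no difference as the absence of one. The items as described support neither statement.

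A later analysis plan cannot repair this. It can choose how to analyse the items, but it cannot add content that was not collected, and the outcome name, objective, hypothesis and instrument are all set in the Protocol.

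**Working it through.** No arithmetic bears on this point. The check sets the passages side by side.

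1. **Construct promised.** The Synopsis, Section 3.2, Table 2, Table 4 and the Section 10.3 hypotheses name parenting self-efficacy: five places, one label.

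2. **Construct described.** Table 2 gives a stem and three examples. The stem refers to the mother's life so far. The examples are getting what she wants from life, feeling in control, and being able to run her life. None of the four mentions the child, parenting or confidence in caring.

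3. **Could another measure carry the hypothesis?** The closest rows of Table 2 are:

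| Measure | Content described | Covers confidence as a parent? |
|---|---|---|
| Parenting styles | Warmth, hostility, inconsistency or irritability | No: reported behaviour |
| Parenting Wellbeing Index | Satisfaction with life domains | No |
| Health literacy | Knowledge, attitudes and beliefs on paediatric health | No |
| Primary outcomes | Nutrition, safety, sleep, responsivity, home environment, child language | No |

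No measure is described as covering it.

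4. **Which reading fits the rest of the Protocol?** The unqualified self-efficacy in Section 10.3 (model covariates) and Section 6.2 (cited predictors) agrees with the described items, not with the outcome label. Table 4 schedules only one self-efficacy measure, and it is collected at enrolment. The covariate and the outcome are therefore presumably the same items under two names. That is an inference; the Protocol does not say so.

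5. **Evidence set aside.** Collection at enrolment, when some women have no child yet, does not show that the measure is general. Table 4 also schedules Parenting styles at enrolment, and Section 10.3 foresees restricting analyses of current parenting to a subgroup for that reason.

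6. **Reach.** Table 2 has ten maternal secondary rows; this is one of them. The sample size in Section 10.1 and the three primary outcomes do not depend on it.

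**The case against.** The strongest reply is that this is loose naming, with the content disclosed beside the name. Table 2 says plainly what the items ask, and the Parenting Wellbeing Index in the same table is likewise described in terms of general life satisfaction. Parenting may simply mean completed by the parent. A report that repeats the Table 2 description would not mislead. This stands in part. It shows that the fault is one of label and that a wording change can cure it. It does not cure the hypothesis in Section 10.3, which states the parenting construct without the description.

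A second reply is that the item list is incomplete. The examples are offered only as examples, and the baseline measures (Appendix 4) and the baseline questionnaire (Appendix 20) are not shown. This stands. A reader might infer that the trial collects no parenting-confidence data at all, or that the hypothesis cannot be tested. The Protocol does not support that: unlisted items cannot be excluded, although the stem makes them unlikely. If they exist, Table 2 misdescribes the measure and still needs correction.

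A third reply is that a general sense of control is a reasonable outcome here. This also stands. Section 5.1.1 has the nurse strengthen coping, problem solving and the use of resources, and Section 6.2 cites low self-efficacy as a predictor of child outcomes. A reader might infer that the measure is a poor choice because life control depends on circumstances outside the program's reach. Nothing in the Protocol says so. The measure may be kept; only its name and the conclusion attached to it need to change.

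**Conclusion.** The mismatch is real and stands on the face of the Protocol. As described, the outcome measures general self-efficacy, no other listed measure covers confidence as a parent, and the secondary hypothesis of improved parenting self-efficacy has no matching measure. A result reported under the present label would support a conclusion about the wrong construct.

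A reader might go further and infer that any result is bound to be misread. That is too strong: a result reported as general self-efficacy or sense of control would be read correctly.

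The conclusion assumes that the Table 2 description fairly represents the whole item set, which cannot be confirmed without the appendices. The point is minor. It affects one secondary outcome; the primary analyses and the sample size are unaffected.

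**What to change.** Check the item set in the study questionnaires, then do one of two things.

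- **If all items concern the mother's own life:** rename the outcome general self-efficacy (sense of control) in the Synopsis, Section 3.2, Table 2, Table 4 and the Section 10.3 hypotheses, and limit the conclusion to that construct. This agrees with the unqualified term already used in Section 6.2 and in the covariate list of Section 10.3. The Synopsis must be included, or the change creates a new inconsistency.
- **If some items concern confidence as a parent:** correct the Table 2 description to say so, and test the parenting hypothesis on those items only.

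The cost is wording, submitted as a modification. With renaming alone, the trial gives up a claim about parenting self-efficacy. Adding a parenting-confidence scale at the 1-year and 2-year visits would keep that claim, but it is optional: it adds to participants' burden, which Section 4.4 names as a criterion in choosing measures.

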## 5. STUDY TREATMENTS

### 5.1 Treatment Arms

#### 5.1.1 Description

**Service design concept:** Right@home has been designed as a proportionate (i.e. higher dose and intensity) service response from the universal maternal and child health services in Victoria and Tasmania. As such, the intervention embeds the universal aspects of the existing service system. In Victoria there are ten Key Ages and Stages consultations recommended to review a child's health, growth and development from birth to 3 ½ years. These include: a home visit and consultations at 2, 4 and 8 weeks, 4, 8, 12 and 18 months, 2 and 3 ½ years of age for all children and their families.

In Tasmania the local Child and Family Health Nurses offer child health and development checks at similar time points, the only difference is that a 6 weeks medical check is recommend and there is no check between 18 months and 3 ½ years.

**Intervention group:** The MECOSH program (see detailed manual in **Appendix 5**) is the foundation for the right@home program. Built onto the MECOSH program are a number of evidence-based strategies that are intended to directly impact the three primary outcomes. These evidence-based strategies, termed 'focus modules', were identified in another recent CCCH literature review, informed by the ERG and reflect best national and international practice. They include strategies on infant sleep training; nutrition; safety; regulation; attachment and social support; and video feedback and

motivational interviewing techniques. The extra modules are currently being incorporated into the right@home program and will be finalised by early March 2013 (see draft addendum to manual in Appendix 6, attached in confidence).

The intervention group will receive at least 25 home visits (actual number of visits determined by need) primarily by the same SNHV program nurse during the remainder of pregnancy and the first 2 years post birth. The nurse will be provided with clinical supervision and each group of nurses (up to 4) will be supported by a dedicated social care practitioner for them and their families. Staff and resources for the intervention will be funded by the industry partners and managed by ARACY and CHETRE. The SNHV nurses are MCH nurses who have received additional training in the intervention program, operating within a distinct SNHV team. Each nurse will be expected to have Family Partnership Training (see <http://www.fpta.org.au/>). The first six right@home nurse training modules are described in **Appendix 7** (attached in confidence).

The home visits are standardised as follows:

- a) Antenatal and postnatal care in accordance with the MCH and MESCH guidelines: antenatal home visits at least 2nd weekly and postnatal visits within one week of birth, and then at least weekly until 6 weeks; second weekly till 12 weeks; monthly to 6 month; bi-monthly until 2 years.

The content of home visits will predominantly focus on evidence-based strategies underpinning the three primary outcomes: the care of child, responsivity to child, and providing a supportive home environment.

The content of each home visit will be individually tailored to each mother's needs, skills, strengths and capacity. Guided by a strengths-based approach and goal setting, the nurse will support and enable the mother and the family to:

- enhance their coping skills, problem solving skills and ability to mobilise resources;
- foster positive parenting skills;
- support the family to establish supportive relationships in their community;
- mentor maternal-infant bonding and attachment; and
- provide primary health care and health education, including but not limited to evidence-based information regarding immunisation, Sudden Infant Death Syndrome (SIDS) risk reduction, infant nutrition and child safety.

- b) Postnatal Learning to Communicate program consisting of 12 monthly sessions commencing when the baby is one month old and finishing when the baby is 12 months old, which include information and activities for parents to encourage child development. Sessions 1-5 are delivered individually during the home visits. Sessions 6-12 are delivered in a group environment. The effectiveness of the Learning to Communicate program has been demonstrated in an unpublished controlled trial, and is a published clinical resource used by clinicians throughout Australasia.

- c) Access to early childhood health services, volunteer home visiting services and family support services.
- d) Group activities and community links including parenting group and walking group specifically for intervention families, and linking into community activities.

The intervention incorporates the standard Key Age and Stage (KAS) visits described in the Service Design Concept above. Existing MECOSH nurse visit checklists (see examples in Manual in **Appendix 5**) will be modified to include statements regarding the need to do KAS at the appropriate times.

**Usual care (control) group:** The control group receive the usual care; that is:

- a) Antenatal care according to MCH protocols, which include:
  - One postnatal home visit by a nurse from the regular child and family nursing service (within 2 weeks of baby's birth)
  - Additional postnatal home or clinic visits with the regular child and family nursing service as indicated by protocols in usual care.
- b) Volunteer home visiting services and family support services within the postcode area as available

Being in the right@home study (both control & intervention) will not preclude access to other support services, except for being part of the Cradle to Kinder (CtK) programs (see Exclusion Criteria, Section 6.2).

Hence the key differences between the right@home intervention and usual care are:

- Home visiting commencing antenatally;
- Continuity of care by the same nurse throughout the 2½ year program;
- Care by nurses with additional training in the right@home and MECOSH program model;
- Standardised postnatal home visiting program to the child's second birthday;
- More frequent, sustained and responsive visits in right@home
- Dedicated social care practitioner;
- Learning to Communicate program and specialised toolkit of focus modules;
- Group activities and proactive links to community activities.

